## Abstract

**Objective:**

To evaluate the effect of a pharmacist‑led educational intervention on medication knowledge, adherence, and asthma control among adult asthma patients at Ayder Comprehensive Specialized Hospital, Ethiopia.

**Methods:**

A single‑blind, parallel‑group randomized controlled trial will be conducted. All eligible adult asthma patients on active follow‑up at the chest clinic of Ayder Comprehensive Specialized Hospital will be included. Participants will be randomly assigned via a computer‑generated sequence to an intervention group (structured pharmacist‑led education using teach‑back, illustrated pamphlets, a follow‑up phone call and SMS) or a control group (routine care). Outcome assessors will be blinded to group allocation. Outcomes will be measured at baseline and after three months, including medication adherence (GMAS), asthma control (ACT), medication knowledge, correct inhaler technique, and domain‑specific adherence barriers. Data will be analyzed using intention‑to‑treat with multivariable binary logistic regression, chi‑square tests, independent T-test, McNemar test, Mann‑Whitney U test, and Fisher’s exact test where appropriate. Subgroup analyses will be performed to explore whether the intervention effect differs across patient characteristics. A p‑value < 0.05 will be considered statistically significant, with 95% confidence intervals reported.

**Trial registry:**

Pan African Clinical Trials Registry (PACTR202508565637179).

## Introduction

Asthma is a persistent inflammatory condition of the respiratory tract that impacts more than 339 million individuals globally [1,2]. Although the condition is more common in wealthy nations [3], its impact is rising notably in developing countries, including Ethiopia, where the estimated prevalence among hospital attendees is 9% [4].

Effective asthma treatment is primarily built on attaining and sustaining proper symptom management [2,5]. Global clinical recommendations, such as those issued by the Global Initiative for Asthma (GINA) [2], highlight the necessity of regular controller treatments, notably inhaled corticosteroids (ICS), for decreasing airway swelling and averting acute episodes [6,7]. Nevertheless, merely prescribing these potent drugs is insufficient; their effectiveness relies fully on the correct usage by patients [8,9].

Consequently, poor adherence to prescribed medications represents a major obstacle, acknowledged as a leading cause of unsatisfactory asthma outcomes [10,11]. In the context of asthma, non‑adherence is a multifaceted issue involving faulty handling of inhaler equipment [12–14], which lowers pulmonary drug deposition [15], and irregular timing or dosing [16], where patients fail to take medicines as often as directed [17]. Research consistently reveals that non‑adherence to controller drugs can reach up to 70%, resulting in inadequate symptom control [5], more frequent emergency visits [18,19], hospital admissions [20], and preventable deaths [21]. In the Ethiopian setting, published figures place non‑adherence to inhaled therapies between 19.1% and 40.8% [4].

A marked shortage of patient understanding about the illness and its treatment often leads to unsatisfactory asthma management [22]. Numerous patients do not clearly comprehend the roles of their drugs, especially the difference between controllers and relievers [16]. Moreover, a large share of patients exhibits improper inhaler handling [17], with certain investigations reporting mistake rates over 50% [14,23]. Faulty inhaler technique is linked to below‑therapeutic drug delivery to the lungs [24], making even the strongest medicines ineffective [25]. This mix of inadequate knowledge and incorrect administration can produce a cycle of treatment failure [26], patient disappointment [27], and reduced confidence in the prescribed regimen [28,29].

Pharmacists, being among the most reachable health professionals, are ideally situated to interrupt this cycle [30,31]. Educational initiatives led by pharmacists have become a promising approach to address knowledge deficiencies and improve medication taking behavior [1,32]. Such organized programs extend beyond routine dispensing to offer thorough counselling on the nature of the disease, the purposes of different drugs, hands‑on training in inhaler use, and methods to overcome adherence barriers [30,33,34]. By focusing on the underlying causes of non‑adherence, knowledge gaps, and skill limitations, these interventions have proven successful in boosting adherence and subsequently enhancing asthma symptom control [35,36].

Although several Ethiopian studies have recorded the high frequency of poor medication knowledge, inaccurate inhaler technique, low adherence, and inadequate asthma control, evidence regarding the effectiveness of pharmacist‑led programs to remedy these problems remains scarce. Therefore, this trial aims to assess the effect of a structured, pharmacist‑led educational intervention on medication knowledge, inhaler technique, adherence, and asthma symptom control in adult asthma patients attending Ayder Comprehensive Specialized Hospital.

## Methods

### Study design

This study is a single‑blind, parallel‑group randomized controlled trial (registered with the Pan African Clinical Trials Registry; PACTR202508565637179). It is a non‑pharmacological, behavioral intervention study, with a total of 131 eligible patients enrolled (all eligible patients from the target population). Screening, intervention, and assessment were conducted at the Chest Clinic of Ayder Comprehensive Specialized Hospital (ACSH). A SPIRIT schedule of enrollment, interventions, and assessments can be found in Figure S1. This protocol has been developed following the Standard Protocol Items: Recommendations for Interventional Trials (SPIRIT) guidelines [37].

### Subject recruitment

Participants for the study were recruited from the Chest Clinic of Ayder Comprehensive Specialized Hospital (ACSH). To ensure recruitment of the target sample size, the research team consecutively screened and approached all eligible asthmatic patients attending the clinic during the recruitment period. Potential participants who met the inclusion criteria received a detailed explanation of the study’s purpose, procedures, potential benefits, and risks. Those who provided written informed consent were enrolled and randomized into the trial.

### Sample size

A formal a priori sample size calculation was not performed because the study aimed to include the entire eligible population. The final sample consisted of 131 adult asthma patients. A post‑hoc power analysis was conducted using parameters derived from published studies in low‑income countries. Based on a meta‑analysis of adherence in Ethiopian asthmatic patients, the pooled baseline adherence is approximately 40% [4]. A clinically meaningful improvement of 20 percentage points (to 60%) was considered, consistent with pharmacist‑led intervention studies in Nigeria [38] and Vietnam [1]. Using a two‑proportion test with α = 0.05 (two‑sided) and a sample size of 131 (approximately 65 per group), the study achieves 80% power to detect an absolute difference of 20 percentage points.

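### The 40% baseline adherence behind the power statement does not fit the non-adherence range that the Introduction takes from the same reference, and the stated 80% power does not hold at 40% or at 60%

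*Protocol article*

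**What the plan says.** The Sample size section of the protocol article says that no a priori calculation was made, because the whole eligible population was to be enrolled. It gives a post-hoc power statement instead, with these inputs:

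- Baseline, from a meta-analysis in Ethiopian patients cited as reference 4: "the pooled baseline adherence is approximately 40% [4".
- Effect: "A clinically meaningful improvement of 20 percentage points (to 60%) was considered".
- Test: two proportions, "α = 0.05 (two‑sided", with "a sample size of 131 (approximately 65 per group".
- Result: "the study achieves 80% power to detect an absolute difference of 20 percentage points".

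The Introduction cites the same reference for the Ethiopian setting, but for the opposite quantity. There, published figures for non-adherence are placed "to inhaled therapies between 19.1% and 40.8% [4".

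Under Statistical analysis, the primary outcome is dichotomized adherence compared by chi-square test. Under Outcome measures, adherent means a GMAS score of at least 27.

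**The concern.** One source is cited for two figures that point in different directions. Adherence of 40% means non-adherence of 60%, which is 19.2 points above the top of the Introduction's range (60 − 40.8). Read the other way, the Introduction implies adherence of at least 59.2%, almost the 60% that the Sample size section treats as the level reached after the intervention.

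The 40% is the baseline of the only power statement in the article, and that statement concerns the primary outcome. If the true level in this population is nearer to the Introduction's figures, the 40% to 60% scenario does not describe the trial, and at the top of that range a 20-point gain has no room. The power statement will also colour how a null result is read, and with recruitment complete the sample can no longer grow to compensate.

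**Working it through.** **Step 1. Put both figures on one scale.** Adherence = 1 − non-adherence.

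- Introduction: 1 − 0.408 = 0.592 and 1 − 0.191 = 0.809, so adherence of 59.2% to 80.9%.
- Sample size: adherence of about 40%, so non-adherence of about 60%.

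The 40% lies outside 59.2% to 80.9%. It is numerically close to the upper non-adherence figure of 40.8%.

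**Step 2. Reproduce the stated power.** Inputs from the Sample size section: p1 = 0.40, p2 = 0.60, two-sided α = 0.05, n = 65 per group. No dropout is applied, as none is stated there. With p̄ = (p1 + p2)/2,

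power = Φ{ [ |p2 − p1| − 1.96 √(2p̄(1 − p̄)/n) ] / √([p1(1 − p1) + p2(1 − p2)]/n) }.

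- Standard error under no difference: √(2 × 0.5 × 0.5/65) = 0.0877.
- Standard error under the alternative: √((0.24 + 0.24)/65) = 0.0859.
- (0.20 − 1.96 × 0.0877)/0.0859 = 0.327, and Φ(0.327) = 0.628.

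Power is 62.8%, or 63.2% with 65.5 per group, against the stated 80%. Other methods do not close the gap:

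| Method | Power |
|---|---|
| Unpooled variance | 64.3% to 64.7% |
| Arcsine | 63.5% |
| Exact chi-square (66 and 65) | 64.8% |
| Fisher's exact (66 and 65) | 58.1% |
| Continuity correction | 55.9% to 56.3% |
| One-sided 0.05 (not what is stated) | 74.2% to 74.5% |

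For 80% power at 40% against 60%, 97 per group are needed (194 in total), or 107 per group with continuity correction.

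**Step 3. Same formula, absolute 20-point gain, other baselines.** Power is for 65 per group. The detectable difference is for 80% power with 65.5 per group.

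| Baseline | Target | Power | Needed per group for 80% | Detectable difference |
|---|---|---|---|---|
| 40% | 60% | 62.8% | 97 | 24.3 points |
| 59.2% | 79.2% | 69.9% | 83 | 22.2 points |
| 60% | 80% | 70.6% | 82 | 22.1 points |
| 70% | 90% | 82.1% | 62 | 19.5 points |
| 80.9% | 100.9% | impossible | – | 15.5 points |

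At 65.5 per group the powers are 63.2%, 70.3%, 70.9% and 82.4%. The 80% figure is first reached somewhere between baselines of 65% (75.5% at 65 per group) and 70%.

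**Step 4. A sensitivity assumption that the protocol does not make.** Going from 40% to 60% is an odds ratio of (0.6/0.4)/(0.4/0.6) = 2.25. If that ratio, rather than the 20-point difference, carried over to higher baselines (65 and 66 per group):

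| Baseline | Target | Difference | Power |
|---|---|---|---|
| 59.2% | 76.6% | 17.4 points | 56.8% |
| 70% | 84.0% | 14.0 points | 47.8% |
| 80.9% | 90.5% | 9.6 points | 34.8% |

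These figures only show how far the answer depends on the form of the effect. They are not the protocol's scenario.

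**The case against.** Four arguments stand against this point.

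*The swap is not proved.* A reader might infer that the 40.8% non-adherence figure was copied in as adherence, or argue that a pooled value cannot fall outside the range it pools. The article supports neither as a certainty. The Introduction speaks of published figures for inhaled therapies and does not say that these are the studies pooled in reference 4. The Sample size section speaks of adherence in asthma patients without that restriction. Nor is it shown that either figure used the GMAS cut-off. The Sample size section may be the correct one: the Introduction also reports non-adherence to controllers of up to 70%, though not for Ethiopia in particular. This objection stands. What remains is an unexplained mismatch.

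*A higher baseline helps.* A reader might infer that a baseline of 59% to 81% leaves the trial with less power. On the protocol's own absolute 20-point effect the reverse is true wherever the gain is possible. The lower powers in Step 4 need an odds-ratio assumption that the protocol does not make, and impossibility affects only the last 0.9 points of the implied range. This stands as well.

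*The figure drives nothing.* The calculation is post hoc, enrolment is complete at 131, and the 40% enters no planned analysis. This lowers the severity, but the published power statement still rests on an input that the article itself contradicts.

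*An article condenses the full protocol.* That would excuse an omission. It does not excuse two stated figures that disagree.

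**Conclusion.** The mismatch is real and can be seen in the article alone: reference 4 is cited for non-adherence of 19.1% to 40.8% and for adherence of about 40%, with no explanation. The 40% baseline is therefore unsupported as written. Which section is wrong, or whether the definitions differ, cannot be decided without the source.

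The power statement needs restating in either case. On the protocol's absolute 20-point effect, with about 65 per group, a two-sided 0.05 test and no dropout, power is about 63% from 40%, 70% from 59.2%, 71% from 60% and 82% from 70%. The stated 80% holds neither at the protocol's own baseline nor if the two rates are exchanged.

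This should be fixed, but it does not threaten the trial's validity: the sample size, endpoint, test and estimate are all unaffected.

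**What to change.** 1. Check reference 4. Correct the Introduction or the Sample size section, whichever is wrong. If both are right, state the difference in definition (inhaled therapies against all asthma medication, instrument, cut-off) and justify the one used for the baseline.
2. Restate power, and the difference detectable with 80% power, for about 65 per group at the corrected baseline, naming the formula. If 40% is confirmed, that means about 63% power for 20 points and a detectable difference of about 24 points.
3. If a constant odds ratio of 2.25 is shown, label it as an added sensitivity assumption.
4. Optionally, once the data are cleaned, tabulate the baseline proportion with GMAS of at least 27 in all 131 patients together, without regard to arm, and report it beside the literature value. Under Trial status, cleaning and coding have not begun, so this check must wait for them and is not needed for the correction.

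The cost is a look at the source, a few sentences and one recalculation. The likely downside is a less favourable stated power. Nothing in the conduct or the primary analysis changes.

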### Randomization

All participants who provide written informed consent and meet the eligibility criteria will be randomly assigned in a 1:1 ratio to either the intervention group or the control group. A block randomization method will be employed using a computer‑generated random number sequence prepared by an independent investigator who is not involved in participant recruitment or intervention delivery. The allocation sequence will be concealed from the research team enrolling participants using sequentially numbered, opaque, sealed envelopes.

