### Statistical analysis

Statistical analysis will be performed using SPSS version 28.0. Descriptive statistics will summarize participant characteristics: categorical variables as frequencies and percentages, continuous variables as means with standard deviations or medians with interquartile ranges. The primary analysis will follow the intention‑to‑treat principle, analyzing all participants according to their original randomized group regardless of whether they completed the intervention. For the primary outcome (dichotomized medication adherence), the proportion of adherent participants will be compared between groups using the chi‑square test. Within‑group changes from baseline to follow‑up will be tested using McNemar test. Between‑group differences at follow‑up will be analyzed using Pearson’s chi‑square test (or Fisher’s exact test when expected cell counts are < 5). For continuous variables with skewed, the Mann‑Whitney U test will be used. Multivariable binary logistic regression will be employed to identify factors associated with poor medication knowledge, medication non‑adherence, and uncontrolled asthma, with the intervention group as the main independent variable adjusted for potential con-founders (age, sex, education, income, Comorbidities, exacerbation history, and smoking status). Effect sizes will be reported as adjusted odds ratios with 95% confidence intervals. Subgroup analyses will be performed to explore whether the intervention effect differs across patient characteristics (age, gender, education, occupation, income, GINA step, comorbidity, exacerbation history) using logistic regression with interaction terms; p‑values for interaction will be reported. Missing data will be handled by complete case analysis if the proportion is low (<5%); otherwise, multiple imputation will be considered. A p‑value < 0.05 will be considered statistically significant.

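### The stated 80% power for a 20-point difference is wrong: 131 patients (about 65 per group) give about 63% power for 40% versus 60%

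*Protocol article*

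**What the plan says.** The Sample size section of the protocol article says that no calculation was made in advance, because the whole eligible population was to be included. It then reports a power analysis with parameters from published studies:

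- Baseline rate: "the pooled baseline adherence is approximately 40" percent.
- Target effect: an "improvement of 20 percentage points (to 60%) was considered", described as clinically meaningful.
- Test and size: a two-proportion test at two-sided alpha 0.05, with 131 patients split into groups of about 65.
- Conclusion: "the study achieves 80% power to detect an absolute difference of 20 percentage points".

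Other sections agree with these inputs. Study design describes the trial "with a total of 131 eligible patients enrolled". Under Randomization, patients are "randomly assigned in a 1:1 ratio to either the intervention group or the control group". For the primary outcome, dichotomised adherence, the Statistical analysis section says that "the proportion of adherent participants will be compared between groups using the chi‑square test". The Sample size section makes no allowance for loss to follow-up.

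**The concern.** Comparing 40% with 60% is close to the hardest case for detecting a 20-point difference, because the binomial variance is largest near 50%. A trial of 131 patients is small for that comparison, so 80% looked too high.

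This figure is the only quantitative statement about the adequacy of the sample. If it is too high, readers will give a non-significant primary result more weight than it can bear. They will believe that a true 20-point benefit would have been missed one time in five, when the real risk is much larger. The Strengths and limitations section does not mention limited power, so nothing elsewhere in the article corrects the impression.

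**Working it through.** **Inputs, all from the protocol article**

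- p₁ = 0.40, p₂ = 0.60, difference d = 0.20 (Sample size)
- two-sided alpha 0.05, so z = 1.960 (Sample size)
- 131 patients, 1:1, so n = 65 or 66 per group, average 65.5 (Sample size, Randomization)
- unadjusted comparison of two proportions by chi-square (Sample size, Statistical analysis)
- stated power: 80%

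**Step 1. Attempt to reproduce the 80%.** The pooled-variance formula, with p̄ = 0.50, is

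Power = Φ{ [d − z·√(2p̄(1−p̄)/n)] / √([p₁(1−p₁) + p₂(1−p₂)]/n) }

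For n = 65:

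- null standard error: √(0.50/65) = 0.0877, and 1.960 × 0.0877 = 0.1719
- alternative standard error: √(0.48/65) = 0.0859
- Power = Φ[(0.2000 − 0.1719)/0.0859] = Φ(0.327) = **62.8%**

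The same formula gives 63.2% for n = 65.5 and 63.5% for n = 66. The stated 80% is not reproduced.

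**Step 2. Other methods with the same inputs**

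| Method, two-sided alpha 0.05, 40% vs 60% | Power |
|---|---|
| Pooled variance, 65 to 66 per group | 62.8% to 63.5% |
| Unpooled variance, 65 to 66 per group | 64.3% to 65.0% |
| Arcsine, 65 to 66 per group | 63.2% to 63.8% |
| Continuity-corrected normal approximation, 65 to 66 per group | 55.9% to 56.6% |
| Exact enumeration, uncorrected chi-square, 65 vs 66 | 64.8% |
| Exact enumeration, continuity-corrected chi-square, 65 vs 66 | 58.0% |
| Exact enumeration, Fisher's exact test, 65 vs 66 | 58.1% |

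The shortfall from 80% is about 15 points at best (unpooled formula, 66 per group) and about 24 points at worst (continuity-corrected approximation, 65 per group).

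**Step 3. Could a slip in the inputs explain 80%?**

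- One-sided alpha 0.05, contrary to the text: 74.2% to 74.7% (pooled).
- 131 read as the size of each group: 90.4%.
- A one-sample test with n = 65: 90.8%.
- 60% versus 80%, as if the 40% were non-adherence: 70.9% (65.5 per group).

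None of these gives 80%.

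**Step 4. What 80% power requires.** With z₀.₈ = 0.8416,

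n = [1.960·√0.50 + 0.8416·√0.48]² / 0.20² = (1.3859 + 0.5831)² / 0.04 = 3.877/0.04 = 96.9

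This means **97 per group, 194 in total**, against 131 enrolled. With continuity correction it is 107 per group, 214 in total.

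**Step 5. What 131 patients can detect.** With 40% under control and 65 to 65.5 per group, pooled power is 78.9% to 79.2% at 24.0 points and 80.6% to 80.9% at 24.5 points. The difference detectable with 80% power is about **24.3 points**, that is, 40% to about 64%.

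**Step 6. Effect of loss to follow-up (assumed; the article gives no rate).** With 10% loss, 131 × 0.90 ≈ 118, or 59 per group:

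Power = Φ[(0.2000 − 1.960·√(0.50/59)) / √(0.48/59)] = Φ[(0.2000 − 0.1804)/0.0902] = Φ(0.217) = **58.6%**

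**The case against.** The strongest reply accepts the arithmetic and disputes its reach.

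- **The figure did not set the sample size.** Everyone eligible was enrolled and recruitment is over, so the error changes neither the number of patients nor the validity of the primary analysis. That is true, and it is why only the text needs to change. But the calculation uses external planning values, not trial results, and the Trial status section says that analysis has not begun. The figure will still shape how the result is read.

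- **The 40% is itself uncertain.** The Introduction cites the same reference for Ethiopian non-adherence to inhaled therapies of 19.1% to 40.8%, which implies adherence of 59.2% to 80.9%. The two figures may differ in scope. Power for a 20-point gain depends on the starting rate: at 65.5 per group it is 70.9% for 60% versus 80% and 82.4% for 70% versus 90%. So 63% should be presented as conditional on 40% under control, and the two figures should be reconciled. This does not rescue the statement, which names 40% and 60% explicitly.

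- **The 10% loss is not in the article, and a dropout allowance may be left to a fuller document.** This is fair. The 59% illustrates the direction and rough size of the effect and is not part of the error. The Statistical analysis section also allows for multiple imputation when 5% or more of the data are missing, so a complete-case set of 59 per group is not certain.

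- **Nothing says that a null result will be misread, and 95% confidence intervals are already promised.** The article indeed states no such reading. Still, a claim of 80% power invites it, and the effect measure for which the Statistical analysis section specifies intervals is the adjusted odds ratio. A sentence on the risk difference is a modest addition.

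**Conclusion.** The statement is wrong as written and must be corrected. On the article's own inputs, power is about 63% (up to 65% with the most favourable two-sided method), not 80%. The type II error at the sponsor's clinically meaningful effect is about 37% (100 − 63.2 = 36.8), so a true 20-point benefit would be missed more than one time in three.

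The conclusion rests on the stated 40% under control and 60% under intervention, the unadjusted two-sided test, and outcome data on all 131 patients. Only the last of these is an assumption beyond the text, and it favours the trial. The error concerns the primary outcome and makes the trial look better powered than it is. It does not bias the planned analysis.

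**What to change.** In the Sample size section, replace the sentence that claims 80% power with text such as:

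> *With about 65 patients per group, two-sided alpha 0.05 and 40% adherence under control, power is about 63% for a 20-point difference (about 59% if 10% of patients are lost to follow-up, an illustrative assumption). Power of 80% is reached for a difference of about 24 points.*

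Add one sentence saying that a non-significant primary result will be interpreted from the 95% confidence interval of the risk difference and not as absence of effect. At the planning values, that interval extends about 17 points either side of the estimate (1.960 × 0.0859 = 0.168), so it can easily include both no effect and a benefit of 20 points.

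When making the change, also state how the 40% adherence figure relates to the non-adherence range in the Introduction.

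The cost is one or two sentences and a less favourable figure. No extra enrolment is proposed, because recruitment is closed, and the test, the outcome and the conduct of the trial stay as they are.
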